| Study Design            | Placebo controlled trial with random allocation.                                                                                                                                                                                                                                                                                                                                                                                                                                                                                                                                                                                                                                                                                                                                                                   |
| Aims                    | 
Primary: To determine whether topical diclofenac affects clinical outcome after 4 weeks of treatment (VISA-A score).
 
Secondary: To determine if topical diclofenac changes pain, pain threshold, or mechanical properties of the Achilles tendon in subjects with chronic Achilles tendinopathy.
                                                                                                                                                                                                                                                                                                                                                                                                                                                                                       |
| Hypothesis              | Individuals treated with topical diclofenac will have a greater improvement in VISA-A score at 4 weeks than those treated with placebo gel.                                                                                                                                                                                                                                                                                                                                                                                                                                                                                                                                                                                                                                                                        |

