## **6. Study Design**

Placebo-controlled trial, random allocation in a 1:1 ratio.

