## **12. Statistical Considerations and Data Analysis**

The pain pressure threshold measurement will be repeated three times and the two closest measures will be used for analysis. To avoid wind up, we will wait one minute between each measure.

A repeat measures ANOVA will be used to detect the effect of time (0, 4, 12 weeks) or treatment (placebo vs active) on VISA-A score. Paired t-tests will be used to detect changes in pain, pain pressure threshold and tendon stiffness from baseline to 4 weeks. The proportion of individuals who have returned to full activity at the different timepoints will be reported as point estimates with 95% confidence intervals. The global rating of change (Likert scale) will be compared between groups using a Mann Whitney-U test.

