### Sample Size Calculation

We estimate that after 4 weeks, the placebo group will experience a clinically insignificant mean improvement of 5 (SD17) points on the VISA-A, compared to a clinically significant improvement of 15 (SD17) with diclofenac. For a two-sided t-test with alpha 0.05 and power 0.80, the required sample size is 46 per group.

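### Pain, pressure pain threshold and tendon stiffness are tested only before versus after, so the planned tests never compare diclofenac with placebo

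*Protocol*

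**What the plan says.** The design in Section 6 is a "Placebo-controlled trial, random allocation in a 1:1 ratio". The Study Summary states the secondary aim as "To determine if topical diclofenac changes pain, pain threshold, or mechanical properties of the Achilles tendon in subjects with chronic Achilles tendinopathy". Section 10.2 lists three numbered secondary outcomes: four numeric pain ratings, a patient-reported rating of change, and pressure pain threshold with transverse tendon stiffness.

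Section 12 then assigns the analyses:

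- VISA-A: "A repeat measures ANOVA will be used to detect the effect of time (0, 4, 12 weeks) or treatment (placebo vs active) on VISA-A score".
- Pain, pressure pain threshold and stiffness: "Paired t-tests will be used to detect changes in pain, pain pressure threshold and tendon stiffness from baseline to 4 weeks".
- Rating of change: "The global rating of change (Likert scale) will be compared between groups using a Mann Whitney-U test".

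The first and third name the comparison of arms. The second does not, and no other analysis of those measures appears in the protocol.

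**The concern.** A paired t-test sets each patient's 4-week value against that patient's own baseline. Its null hypothesis is zero mean change. Treatment does not enter it, so the randomised control group plays no part in the inference. The secondary aim asks what diclofenac does, and in a parallel trial that requires the contrast with placebo.

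Change without any drug effect is plausible here. Section 9 requires every participant to be in an active rehabilitation programme, and it selects on current severity (VISA-A below 80), which invites regression to the mean. A significant fall in pain in the diclofenac arm could therefore reflect rehabilitation, natural course, placebo response or selection. A significant result in one arm beside a non-significant result in the other is not evidence that the arms differ.

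At stake are two of the three numbered secondary outcomes, and all of the aim on pain, threshold and mechanical properties.

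**Working it through.** **1. The plan's own figure.** The Sample Size Calculation assumes VISA-A improvements of 5 and 15 points, SD 17 in each arm, two-sided alpha 0.05 and power 0.80. The normal formula gives n per arm = 2 × (1.96 + 0.842)² × (17/10)² = 45.4, rounded up to 46. This matches the stated 46; the exact t-based value is 46.35, so 47. The figure is not in dispute. It is a between-arm calculation for VISA-A and says nothing about the paired tests.

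**2. What the paired test detects when the drug does nothing.** Inputs:

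- n = 50 per arm (100 participants at 1:1) and two-sided alpha 0.05.
- The same true mean change in both arms, so no drug effect.
- Standardised change d (mean change divided by SD of change). The protocol gives neither term for pain, threshold or stiffness, so d is an assumption. The range is 0.2 to 0.5. The middle value borrows the VISA-A placebo assumption, "the placebo group will experience a clinically insignificant mean improvement of 5 (SD17) points on the VISA-A", which gives 5/17 = 0.29.

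The probability of a significant result is P(|T| > t₀.₉₇₅,ₙ₋₁), where T is noncentral t with n − 1 degrees of freedom and noncentrality d√n. For n = 50 the noncentralities are 0.2 × 7.07 = 1.41, 0.294 × 7.07 = 2.08 and 0.5 × 7.07 = 3.54. Call the single-arm probability p. The arms are independent, so a significant diclofenac arm with a non-significant placebo arm has probability p(1 − p).

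| Equal true change in both arms | Diclofenac arm significant, n = 50 | Pooled test significant, n = 100 | Diclofenac significant, placebo not |
|---|---|---|---|
| 0.2 SD | 28% | 51% | 0.284 × 0.716 = 20% |
| 0.29 SD | 53% | 83% | 0.531 × 0.469 = 25% |
| 0.5 SD | 93% | >99% | 0.934 × 0.066 = 6% |

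With 46 analysed per arm, the single-arm figures are 26%, 50% and 91%, and the last column is 19%, 25% and 8%.

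**3. The alternative.** When both arms change equally, a between-arm test is significant 5% of the time whatever the common change. For a standardised difference of 10/17, a two-sample t-test has about 80% power with 46 per arm and 83% with 50. Power for pain, threshold and stiffness cannot be computed, because the protocol gives no effect size or SD for them.

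**The case against.** **The sentence may be shorthand, or the detail may be in the SAP.** A SAP may exist and could add a comparison. But the protocol does not defer here: it names a test. The sentences on either side specify the arms where a comparison is meant. Paired tests would suit a crossover such as the pilot described in Section 2, but this trial is parallel.

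**The effect on the trial is limited.** This stands. The only hypothesis and the sample size concern VISA-A at 4 weeks. The numbered aims in Section 3 are framed against placebo: the first names VISA-A, and the second concerns 12 weeks, when VISA-A is the only scale collected. The aim on pain, threshold and mechanical properties is stated only in the Study Summary.

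**Stronger readings that the document does not support:**

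- A reader might infer that the type I error is inflated from 5% to 53%. It is not. For a null of zero change, 53% is correct power when the true change is 0.29 SD. It misleads only if the result is taken as a drug effect, and Section 12 does not say it will be.
- A reader might infer that the plan expects these three measures to improve on placebo. It says so for VISA-A only. Nothing in it shows that stiffness would change on placebo.
- A reader might take 25% as typical. It is essentially the ceiling, since p(1 − p) cannot exceed 0.25.
- A reader might extend the point to return to activity, for which proportions "returned to full activity at the different timepoints will be reported as point estimates with 95% confidence intervals". That is not a listed secondary outcome. Descriptive proportions with intervals are legitimate, and the wording does not exclude reporting by arm.

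**Conclusion.** The point holds for the four pain ratings, pressure pain threshold and tendon stiffness. The stated tests measure change over time, and no version of them, per arm or pooled, estimates or tests the effect of diclofenac against placebo. This follows from the form of the test and the parallel design, and needs no numerical assumption.

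The percentages illustrate how easily the results could be misread. They rest on equal change in both arms, full analysis of 50 per arm and an assumed standardised change, and they are not error rates of the plan. The VISA-A analysis, the global rating and the sample size are untouched by this sentence. The defect should be corrected before any data are analysed, because a SAP that followed Section 12 would inherit it.

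**What to change.** Replace the paired t-test sentence in Section 12 with a between-arm comparison for each pain rating, pressure pain threshold and stiffness. ANCOVA of the 4-week value on treatment, adjusted for the baseline value of the same measure, is preferable; report the adjusted difference with its 95% CI. A between-arm comparison of change from baseline would also cure the defect. Keep within-arm changes as description, without p-values.

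The cost is one sentence, and the sample size does not change. Threshold and stiffness are already measured at Visit 1 and Visit 2. Pain carries a condition: the Visit 1 procedures do not list the numeric pain ratings, although the existing paired test already presupposes them. Add the ratings to Visit 1, or state where the baseline values come from.

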## **9. Eligibility Criteria**

### **Inclusion Criteria**

1. Male and female subjects aged 19 years and older.
2. Fluent in English.
3. Subjects previously diagnosed with Achilles tendinopathy by a health care professional (imaging at the discretion of the treating physician) and demonstrating the following criteria – localized tendon pain and thickening, worsened with palpation and tendon loading activities, and no clinical suspicion of other diagnoses.
4. Symptoms for 3 months or more.
5. Subjects who are able to give informed consent.
6. VISA-A score less than 80.
7. Subjects who are engaged in an active rehabilitation program prescribed by an exercise specialist

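### The analysis stated for pain, pressure pain threshold and tendon stiffness is a paired test within participants, which cannot answer the secondary aim of whether diclofenac changes them

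*Protocol*

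**What the plan says.** The Study Summary states the secondary aim as an effect of the drug: "To determine if topical diclofenac changes pain, pain threshold, or mechanical properties of the Achilles tendon in subjects with chronic Achilles tendinopathy". Section 6 gives the design: "Placebo-controlled trial, random allocation in a 1:1 ratio". Section 10.2 lists the outcomes that serve this aim: four numeric pain ratings, the PPT and transverse tendon stiffness, together with a global rating of change.

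Section 12 then assigns the analyses. For the primary outcome: "A repeat measures ANOVA will be used to detect the effect of time (0, 4, 12 weeks) or treatment (placebo vs active) on VISA-A score". For the global rating: "The global rating of change (Likert scale) will be compared between groups using a Mann Whitney-U test". For the other six measures: "Paired t-tests will be used to detect changes in pain, pain pressure threshold and tendon stiffness from baseline to 4 weeks". It does not say whether these paired tests are run in each arm or in all participants together. No other section names a comparison of the arms for them.

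**The concern.** A paired t-test asks whether the mean change from baseline differs from zero. Run in each arm or pooled, it does not use the randomised control, so it does not estimate diclofenac minus placebo.

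Change from baseline can also arise without any drug effect. Both arms receive other treatment, because entry requires "Subjects who are engaged in an active rehabilitation program prescribed by an exercise specialist". Placebo response and the natural course of symptoms act in both arms too. For VISA-A the protocol itself plans for this: "the placebo group will experience a clinically insignificant mean improvement of 5 (SD17) points on the VISA-A".

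Two things are at stake. The secondary aim for pain, PPT and stiffness has no stated analysis that can answer it. And the tests that are stated can be significant in the diclofenac arm through change that placebo participants share. Finding one arm significant and the other not is no substitute, because it is not a test of the difference between the arms.

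**Working it through.** **The plan's own figure.** The Sample Size Calculation assumes a VISA-A improvement of 5 (SD 17) on placebo, "compared to a clinically significant improvement of 15 (SD17) with diclofenac", two-sided alpha 0.05 and power 0.80.

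n per group = 2 × (1.960 + 0.842)² × (17/10)² = 2 × 7.85 × 2.89 = 45.4, so 46.

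The stated 46 reproduces. The exact t solution is 46.35, that is 47, a trivial difference. This calculation concerns VISA-A only and does not bear on the point.

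**Inputs for the illustration.**
- n = 50 per arm: 100 participants (Section 8) at 1:1 (Section 6). Also n = 46.
- SD of change 17 and a common change of 5: the VISA-A placebo figures from the Sample Size Calculation, used as an assumption because the protocol gives none for pain, PPT or stiffness.
- Common change varied over 0, 2.5, 5, 7.5 and 10.
- Drug effect zero, so both arms change equally. The arms are independent.

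**Formula.** The paired t statistic has a noncentral t distribution with n − 1 degrees of freedom and noncentrality (change/SD) × √n. For a change of 5 and n = 50 this is (5/17) × √50 = 0.294 × 7.071 = 2.08. Let p be the probability that the two-sided 5% test is significant. The chance that diclofenac is significant and placebo is not is p × (1 − p).

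| Common change (SD 17), inert drug | Diclofenac-arm paired test significant, n = 50 | Same, n = 46 | Diclofenac significant, placebo not, n = 50 | Between-arm test significant |
|---|---|---|---|---|
| 0 | 5% | 5% | 0.05 × 0.95 = 4.8% | 5% |
| 2.5 | 17.5% | 16.4% | 0.175 × 0.825 = 14.4% | 5% |
| 5 | 53.1% | 49.7% | 0.531 × 0.469 = 24.9% | 5% |
| 7.5 | 86.4% | 83.3% | 0.864 × 0.136 = 11.8% | 5% |
| 10 | 98.3% | 97.4% | 0.983 × 0.017 = 1.7% | 5% |

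If the paired test is run on all 100 participants together, it is significant in 30.8% of trials at a common change of 2.5 and in 83.0% at 5.

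The between-arm column is constant because a change shared by both arms cancels in the difference. The fourth column cannot exceed 25%, since p(1 − p) is largest at p = 0.5. The value at a change of 5 is therefore close to the maximum and is not a typical figure.

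**The case against.** The strongest case on the other side has five parts.

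- **Borrowed magnitude.** The common change and SD come from VISA-A. Entry selects on VISA-A below 80 but not on PPT or stiffness, and no section predicts that stiffness changes in four weeks without the drug. The Visit 1 text treats resting pain at testing as uncommon, so the rest-pain items may have little room to fall. This stands. A reader might infer a 53% false-positive rate for these outcomes, but the documents do not support that for any of them. With no common change the rate is the nominal 5%.
- **Interpretation.** A reader might infer that the investigators will present within-arm improvement as a drug effect. No section says how the results will be read. The wording of the secondary aim makes that reading possible, but it remains an inference.
- **Reach.** The numbered aims (Section 3), objective (Section 4) and hypothesis (Section 5) are framed around VISA-A, whose analysis includes treatment. The global rating is compared between groups. The aim for pain, threshold and mechanics appears only in the Study Summary. This limits the point to six secondary measures and leaves the primary result untouched.
- **An unseen SAP, and data that remain usable.** Section 12 does not forbid a further comparison, a SAP may add one, and the randomised data would allow it at any time. That makes the fault easy to cure. It does not make the sentence right: the same paragraph names a group contrast for the two other analyses and a different, within-participant method here, so this is a stated choice and not a detail left open.
- **Baseline pain.** A reader might assume that a baseline-adjusted analysis needs no new data. Visit 1 lists VISA-A, stiffness and PPT but no numeric pain rating, and pain appears only among the Visit 2 measures. Section 12 implies a baseline without providing for it, so the assumption is unconfirmed for four of the six measures.

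**Conclusion.** The method is wrong as written for the four pain ratings, PPT and tendon stiffness. A paired test from baseline to week 4 has no treatment contrast and cannot answer the secondary aim of a placebo-controlled randomised trial. That conclusion rests on the text alone and needs no assumed value.

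The size depends on how much both arms change for reasons other than the drug, which the protocol does not state for these outcomes. On the VISA-A scale, with an inert drug and 50 per arm, the diclofenac-arm test is significant in anything from 5% (no common change) to 98% (a common change of 10) of trials. The pattern of diclofenac significant and placebo not occurs in about 2% to 25%. These figures show the mechanism and do not predict error rates for pain, PPT or stiffness.

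**What to change.** Replace the sentence on paired t-tests in Section 12. For each pain rating, PPT and stiffness, compare diclofenac with placebo at week 4, preferably with a linear model on the week-4 value that has treatment as a factor and the baseline value as a covariate. A two-sample comparison of change would also cure the defect. Report the mean difference with its 95% CI, and give within-arm changes descriptively.

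Reconcile the Visit 1 procedures, which list no baseline pain rating, with Section 12, which needs one. If baseline pain is not collected, compare week-4 pain between the arms without that covariate.

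The cost is one sentence on analysis and a check of the Visit 1 data collection. No extra participants are needed. PPT and stiffness are already measured at both visits. Whether pain needs an added baseline rating depends on the reconciliation. The change should be made before unblinding.

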### Sample Size Calculation

We estimate that after 4 weeks, the placebo group will experience a clinically insignificant mean improvement of 5 (SD17) points on the VISA-A, compared to a clinically significant improvement of 15 (SD17) with diclofenac. For a two-sided t-test with alpha 0.05 and power 0.80, the required sample size is 46 per group.

